**Fig. 1 Fig1:**
[figure not shown]
Study Design: hypothetical data explaining the N-of-1 design based on phase length randomization and additional placebo phases change

The schedule of each random phase transition from each patient will be transmitted to the health care manager responsible for scheduling patients visits and prosthetist’s activity. Participants, care providers and those assessing outcomes will be blind to the placebo or true phase change. Each phase change will be performed by a different prosthetist from the one who manufactured the prosthesis. At true phase transition, a prosthetist will either connect or disconnect Unity and a third prosthetist verify it after the procedure. S/he will not make any changes if no phase transition is expected (placebo transition). However, s/he will ensure that the prosthesis is properly adjusted. It is not possible for the patient to know whether the Unity tube is connected or not (no visual change).

If the patient misses a phase transition visit, the visit will be rescheduled as close as possible to the planned visit, and the modification of phase length notified. At the end of the trial, patients will be allowed to keep the Unity System if they wish, free of charge. In case of unlikely adverse effects in wearing the prosthesis, the trial will end for that particular patient and s/he will return to his usual prosthesis. This is however very unlikely, as before the trial, the patient will wear the prosthesis for 28 days (which will detect any problems before the trial starts). No emergency unblinding is needed as the prosthetist performing the adjustments is not blind and will notify any adverse effects due to the Unity system.

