### Design

After the inclusion visit, a prosthesis (with an Iceross Seal-In™ liner) equipped with an Össur-compatible foot and a Unity system will be manufactured for each included patient. Each center will have one single prosthetist, trained and qualified for the Unity system by the Össur company, who will manufacture all the prosthesis of the trial but will be independent of the team performing the study. Each patient will wear the new prosthesis with the Unity system connected for 28 days, before beginning the N-of-1 trial. This acclimation period is necessary to adjust the prosthesis and obtain a stability in patient’s daily activities.

The N-of-1 trial will then last 50 days for each patient, following a design with random alternation of Unity connection and disconnection of minimum 7 days periods. This minimum period has been decided in order to include a weekend in each period, as patient’s activity level is expected to be variable between weekdays and weekends. Randomization will be performed on R, SCDA (Single Case Data Analysis) plug-in package, by an off-center independent operator. The randomization will use a phase length ABAB randomization (i.e. allowing periods of unequal duration, which allows to interpret results with individual statistical significance) rather than block randomization commonly used in drug trials. “A” is for Unity system disconnected, and “B” for Unity system connected (see Fig. 1). However, because the patient has to come to the rehabilitation center at each phase change which would not allow the patient and the assessors to be blind to the next phase content, phases of a duration >14 days will be further randomized into two half-phases (of 7 days minimum), of the same content i.e. either connected or disconnected. A placebo visit between the two half-phases will allow to keep the blinding. The maximum phase duration obtained by ABAB randomization is 29 days, which will be further randomized to half-phases of minimum 7 days, meaning that the maximum duration of a half-phase is 22 days.

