** Satisfaction and balance questionnaires**	
- Quebec User Evaluation of Satisfaction with assistive Technology (QUEST)^c^ [21, 22]	
- Activities-specific Balance Confidence-Simplified (ABC-S) scale [23]	

^a^*VAS* Visual Analogue Scale

^b^Before and after the prosthetist checks OR connects/disconnects the Unity system

^c^The assessment tool was developed simultaneously in French and English. In French, the assessment is entitled ÉSAT for “Évaluation de la Satisfaction envers une Aide Technique”

Additionally, the app will allow to monitor weekly side effects and factors that may influence the daily ecological outcome measures: patients will answer weekly the two questions: “Have you experienced any unusual event this week that may have affected your prosthesis wearing time, use or comfort (illness, accident, fall, unusual activity, etc.)?” “Have you had an unusual problem with your stump or prosthesis: sweat, wound, unusual pain, abnormal noises from the prosthetic, accidental loosening?”. Responding to all questions has been tested and takes 1 to 3 minutes par day. For patients not familiar with the app, a paper version will be proposed.

For each patient, clinical characteristics will be noted : health status, time of day that data are collected, activity level according to the International Classification of Functioning, Disability and Health (ICF) d4602 and/or d4608 [24], age, and cause of amputation as realized in the study of Sanders et al. [16]. This data will be collected in a paper CRF (with double data entry).

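### The third-prosthetist check is written for true transitions only, so if noticed it marks the real switches: a risk to the blinding that identical verification at every visit would remove

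*Protocol article*

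**What the plan says.** All of this is in the Design subsection of Methods & design unless noted.

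- **Purpose of placebo visits.** Patients attend the centre at each phase change, so longer phases are divided and a placebo visit is placed between the halves to preserve blinding.
- **Blinding claim.** "Participants, care providers and those assessing outcomes will be blind to the placebo or true phase change".
- **True visit.** "At true phase transition, a prosthetist will either connect or disconnect Unity and a third prosthetist verify it after the procedure".
- **Placebo visit.** "S/he will not make any changes if no phase transition is expected (placebo transition"), followed by "However, s/he will ensure that the prosthesis is properly adjusted". No verification step is mentioned.
- **Safeguard offered.** "It is not possible for the patient to know whether the Unity tube is connected or not (no visual change").
- **Visit assessments.** Table 3, footnote b, places them at two times in each visit: "Before and after the prosthetist checks OR connects/disconnects the Unity system".
- **Split rule.** "phases of a duration >14 days will be further randomized into two half-phases (of 7 days minimum"), with the consequence "meaning that the maximum duration of a half-phase is 22 days".
- **Order.** The randomization is of phase lengths in ABAB, and the limitations paragraph of the Discussion confirms that every patient starts with Unity disconnected.

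**The concern.** A placebo visit protects the blinding only if it cannot be told from a true one. The article attaches a second person's check to true transitions and describes no counterpart at placebo transitions. A site that follows the text would have two prosthetists handle the device when the state changes and one when it does not.

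The consequence would be larger than the unmasking of one visit. Because the order is fixed and starts with A, a person who recognises the true switches can reconstruct the condition on every day. The primary outcome is a daily self-rating of comfort, and the Discussion itself accepts that patient-reported outcomes on costly devices can be heavily biased without blinding. The randomization test gives no protection here, since expectation effects that begin at the true switch dates look like a treatment effect at those dates.

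The schedule carries a second, smaller cue. Only phases over 14 days are split, yet a half-phase may last up to 22 days, so an unusually long gap between visits shows that the patient is inside a split phase.

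**Working it through.** **1. The two visit types side by side**

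| Element | True transition | Placebo transition |
|---|---|---|
| Prosthetist's action | connects or disconnects | no change, fit check |
| Third-prosthetist verification | stated | not stated |
| Assessments before and after | yes | yes |
| Visible change in the device | none claimed | none |

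The pronoun in the placebo sentence is ambiguous. If it means the connecting prosthetist, no third prosthetist is described at a placebo visit. If it means the third prosthetist, the connecting one is not described there. Under either reading two people are described at a true visit and one at a placebo visit.

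**2. Reproducing the plan's figures.** Four phases of at least 7 days summing to 50 days give C(25,3) = 2300 assignments, and 1/2300 = 0.0004. The longest phase is 50 − 3 × 7 = 29 days and the longest half-phase 29 − 7 = 22 days. All agree with the article. Four phases mean three true switches inside the 50 days.

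**3. Number of placebo visits.** A given phase exceeds 14 days in 680 of the 2300 assignments (0.296). The mean number of placebo visits per patient is 4 × 680/2300 = 1.18, or 20 × 1.18 ≈ 24 in the trial. By number of split phases, 84 assignments have none (3.7%), 1712 have one (74.4%) and 504 have two (21.9%).

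**4. How often a long interval occurs.** The article does not give the split distribution; equal probability for each allowed cut is assumed here.

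- The first phase has length L in C(31 − L, 2) assignments.
- A phase of length L has L − 13 allowed cuts, and L − 21 of them make the first half longer than 14 days.
- Summing C(31 − L, 2) × (L − 21)/(L − 13) over L = 22 to 29 gives 4.00 + 5.60 + 5.73 + 5.00 + 3.85 + 2.57 + 1.40 + 0.50 = 28.65.
- First interval over 14 days: 28.65/2300 = 1.2% of schedules.
- Any interval over 14 days: 4 phases × 2 halves × 28.65/2300 = 10.0%. These events cannot coincide, since two would need at least 22 + 22 + 7 + 7 = 58 days.

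**5. What visit dates alone reveal.** Full enumeration under the same assumption, for an observer who knows every rule:

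| | As written | Half-phases 7–14 days (14 + 15 for a 29-day phase) |
|---|---|---|
| Any interval over 14 days | 10.0% | 0.17% (4/2300) |
| Patients with at least one visit deducible from past dates | 10.4% | 4.7% |
| Same, with all dates known | 21.6% | 13.0% |
| Patients with every visit deducible, all dates known | 6.3% | 4.0% |
| Best-guess accuracy per visit, at the time | 73.0% | 72.6% |

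Always guessing a true switch is already right for 3/4.18 = 71.7% of visits. A long interval has one placebo and one true boundary, each order equally likely. Only a long first interval settles the matter at once: the visit that closes it must be placebo.

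**The case against.** A reader might infer from the text that patients and assessors can tell the visits apart and that the double-blind claim fails. The case against that inference is strong. The article never says that verification is omitted at placebo visits; it is silent. It does not say that the check takes place in front of the patient or an assessor, and footnote b fixes the timing of assessments without placing assessors in the room. Nobody is said to tell patients that a second check means a real switch. The same paragraph requires blinding, and a site could meet that requirement by checking out of sight. To say that every visit is identifiable needs omission, visibility and an understanding of what the check means, all at once. That stronger reading is not supported.

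The interval cue also needs someone who knows the 14-day rule, and the article does not say that patients or assessors do. Dates raise best-guess accuracy by about one percentage point at the time of the visit. Close to half of the 10.4% remains after the cap, because it comes from a fixed order and a finite trial length.

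What remains is that the verification is explicitly tied to one visit type, in a design whose placebo visits exist to be indistinguishable. The stated safeguard concerns the look of the tube, not who attends or how often the device is handled. This is a rule as written rather than a detail left to a longer document.

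**Conclusion.** The point holds as a risk to blinding from an asymmetric visit procedure. If the extra check is noticed and understood, it identifies the true switches and, through the fixed A-first ABAB order, the condition under which comfort is being rated. How often that would happen cannot be calculated, because the article is silent on visibility; no failure of blinding is shown.

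The interval cue is secondary and minor: about 10% of schedules contain an interval over 14 days and 1.2% begin with one. These percentages rest on equally likely splits and a fully informed observer. Another split distribution would change them, but not the logic that such an interval lies inside a split phase. The case for a change rests on the verification step and on how little it costs to make it uniform.

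**What to change.** **Main change.** In the Design section, state that the third prosthetist carries out the same verification of the scheduled state at every visit, true or placebo, with the same people and the same handling of the device. This removes the cue whether or not the check is visible. It also detects an unintended switch at a placebo visit, for which the article describes no check. The cost is about 24 extra short checks across 20 patients, by a prosthetist already assigned. Stating that the check takes place out of sight of patient and assessor would deal with visibility, but would leave placebo visits unverified.

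**Minor, optional change.** Draw the split only among half-phases of 7 to 14 days, with 14 + 15 days in either order for a 29-day phase. This is one constraint in the half-phase randomization. Phase lengths, the number of visits and the 2300 assignments used by the randomization test stay as they are.

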### Outcome measures

The primary outcome measure is the Prosthetic Socket Comfort Score (SCS), an 11-point numerical scale rated from 0 to 10 [18], based on the question: ‘On a 0 – 10 scale, if 0 represents the most uncomfortable socket fit you can imagine, and 10 represents the most comfortable socket fit, how would you score the comfort of the socket fit of your artificial limb at the moment?’. Test-retest reliability found an intra-class correlation coefficient at 0,79 when the SCS is administered by electronic versions. The minimum detectable change was estimated between 2.73 and 3.26 [19]. The SCS is a validated measure of comfort, commonly used in France but which has never been validated in French; therefore, a French back translation was carried out (appendix 1) to validate the formulation. The SCS will be administered daily by an phone app designed for the study and previously tested for functionality with one patient. It will be recommended to the patient to rate the SCS at a fixed time each day. In case the patient forgets to rate the SCS, s/he will receive a reminder text message between 7pm and 8pm. In case of participant’s low participation in providing their daily SCS, the participant will be phoned by the investigator of the center to increase motivation. Charts of missing data will be updated every month and solution for non-compliant participants discussed with investigators.

Secondary outcomes measures will be collected during the 50 days period of the N-of-1 trial: (1) by the same app, daily for patient-reported limb-prosthesis fitting, stump volume variation, and daily wearing time of the prosthesis (see Table 3); (2) by a pedometer for the number of steps per day; (3) by blind assessors during adjustment visits in the rehabilitation center for the other secondary outcomes listed in Table 3.

**Table 3 Tab3:** Secondary outcomes

**Daily (ecological)**	**Measurements**
**Pedometer**	Number of steps
**Patients-Reported Outcomes Measures (PROMs)**	
- 2 PROMs about indirect assessment of the stump volume variation:	
** 1.a** “How many times have you removed your prosthesis during the day (not counting the evening’s removal) to add compensation sheaths? “	0, 1, 2, 3, 4, >4,
** 1.b** “Did you have the fear at one (or more) moment(s) of the day, of losing your prosthesis, that it would come off by itself? “	VAS^a^: 0 = not at all 10 = yes a lot
- 2 PROMs on the limb-prosthesis fitting:	
** 2.a** “Do you feel in control of your prosthesis, as if the prosthesis is one with you?”	VAS^a^: 0 = not at all 10 = perfectly
** 2.b** “Do you feel pistoning movement of your prosthesis when walking (sensation of vertical movement of the prosthesis because of the stump when walking)?”	VAS^a^: 0 = not at all 10 = yes a lot
- Wearing time of the prosthesis	In hours
**At each phase change visit twice**^b^	
**Functional walking parameters**	
- L-Test [20]	
- 6-minute walk test [21]	
** Satisfaction and balance questionnaires**	
- Quebec User Evaluation of Satisfaction with assistive Technology (QUEST)^c^ [21, 22]	
- Activities-specific Balance Confidence-Simplified (ABC-S) scale [23]	

^a^*VAS* Visual Analogue Scale

^b^Before and after the prosthetist checks OR connects/disconnects the Unity system

^c^The assessment tool was developed simultaneously in French and English. In French, the assessment is entitled ÉSAT for “Évaluation de la Satisfaction envers une Aide Technique”

Additionally, the app will allow to monitor weekly side effects and factors that may influence the daily ecological outcome measures: patients will answer weekly the two questions: “Have you experienced any unusual event this week that may have affected your prosthesis wearing time, use or comfort (illness, accident, fall, unusual activity, etc.)?” “Have you had an unusual problem with your stump or prosthesis: sweat, wound, unusual pain, abnormal noises from the prosthetic, accidental loosening?”. Responding to all questions has been tested and takes 1 to 3 minutes par day. For patients not familiar with the app, a paper version will be proposed.

For each patient, clinical characteristics will be noted : health status, time of day that data are collected, activity level according to the International Classification of Functioning, Disability and Health (ICF) d4602 and/or d4608 [24], age, and cause of amputation as realized in the study of Sanders et al. [16]. This data will be collected in a paper CRF (with double data entry).

### Sample size calculation

#### Power calculation for each N-of-1 trial (i.e. each patient)

One method for calculating power in a single N-of-1 trial (i.e. for a single patient) is calculating the number of possible randomization assignments [25, 26] which depends on the type of randomization, the number of phases and the number of measurements per phase. The greater the number of possible assignments, the greater the possibility of detecting a treatment effect that exceeds the threshold of significance of 0.05 if an effect exists. With 4 true phase transitions, with a minimum duration phase of 7 days, a maximum study duration of 50 days, and 1 measurement per day, the number of assignments generated by this design is therefore 2300, allowing a significance of up to *p =* 0.0004 for each patient, as calculated on R package for single-cases [17].

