### Statistical analysis

#### Statistical analysis of each patient’s N-of-1 trial

Effectiveness of the Unity system regarding SCS and daily secondary outcome measures will be tested by randomization test [20, 28], using the mean of each phase. Randomization allows reliable statistical analysis of auto correlated data (such as data from N-of-1 trials) and allows to extract a statistical effect for each participant separately. Missing data points will be managed by multiple imputation method. In case of a rescheduled transition visit, the real transition date and not the initially scheduled one will be used.

The secondary outcome measures assessed during visits in the rehabilitation center will be analyzed by NAP (Non Overlap of All pairs) [21, 22]. NAP is an estimate of the probability that a randomly selected point in Phase B shows an improvement over a randomly selected point in Phase A with θ=Pr(YB>YA)+0.5×Pr(YB=YA). Since NAP's interpretation of effect size according to Cohen's rules (d=3.464⁎(1√(1-NAP)/.5) has been shown to be inadequate, Parker's criteria will be used [21] (effect present but small if NA*P =* 0.5-.65; moderate effect: .66-.92; large effect: .93-1.0.). NAP [21] will also be applied to daily outcome measures, in addition to randomization tests, to obtain an effect sizes.

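### All 50 days are placed in a phase with no rule for the day of a true switch, so whole-day outcomes mix both Unity states on 3 or 4 days and the step count includes the trial's own walking tests

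*Protocol article*

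**What the plan says.** Under the power calculation for each N-of-1 trial, the article gives "With 4 true phase transitions, with a minimum duration phase of 7 days", then "a maximum study duration of 50 days, and 1 measurement per day, the number of assignments generated by this design is therefore 2300", and puts the smallest attainable p-value per patient at 0.0004. The Design section adds: "The maximum phase duration obtained by ABAB randomization is 29 days".

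The statistical analysis section tests the SCS and the daily secondary outcomes by randomization test "using the mean of each phase". Its only dating rule is that, when a visit is rescheduled, the actual transition date replaces the planned one.

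Connection and disconnection take place at a centre visit. Phases longer than 14 days get an additional placebo visit, at which nothing is changed. Table 3 schedules the L-Test and 6-minute walk test twice per visit, and its footnote b gives the timing: "Before and after the prosthetist checks OR connects/disconnects the Unity system". Steps are collected "by a pedometer for the number of steps per day", and Table 3 lists them among the daily ecological measures. The SCS asks about comfort at the moment of rating, preferably at a fixed time each day. The sheath-removal and fear items, wearing time and the step count refer to the whole day.

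**The concern.** A patient who is switched at a visit spends part of that day connected and part disconnected. If the whole day counts towards one phase, its whole-day values carry some of the other condition, and the difference between connected (B) and disconnected (A) shrinks towards zero. The SCS faces a different risk: a rating given before the visit describes the old state but may be filed under the new one. Phases can be as short as 7 days, so one such day can be a seventh of a phase mean.

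Separately, every visit day contains two rounds of L-Test and 6-minute walk test. Nothing in the article keeps those steps out of an outcome that is meant to describe daily life.

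The possible consequences are some loss of sensitivity in the individual tests and the pooled estimate, and a step count that depends partly on the visit calendar. Each patient receives an individual verdict, so schedule-specific noise matters as well as average bias.

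**Working it through.** **1. Reproducing the article's count.** Inputs from the article: N = 50 days, minimum phase m = 7. With k = 4 phases (ABAB), the number of schedules is C(N − km + k − 1, k − 1) = C(50 − 28 + 3, 3) = C(25, 3) = 2300, and 1/2300 = 0.0004. The longest phase is 50 − 3×7 = 29 days. Both stated figures reproduce, and both require all 50 days to lie in a phase. Four transitions inside the 50 days would mean five phases and C(19, 4) = 3876, which does not match. So there are three internal switches. The fourth transition can only be the disconnection at the start, after 28 connected days of acclimation. The article does not say whether that takes place on day 1.

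**2. Dilution of whole-day outcomes.** Assumptions: the switch day is counted in the new phase, a share f of its value reflects the old state, and B−A is the difference of equally weighted phase means. With phase lengths L1 to L4:

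retained share = 1 − (f/2)(1/L2 + 1/L3 + 1/L4), with 1/L1 added in the bracket if day 1 is a switch day.

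Over the 2300 schedules the mean of 1/L is 0.0906 for each phase.

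| f | Day 1 | Mean retained | Worst schedule | 2 points become |
|---|---|---|---|---|
| 0.5 | clean | 1 − 0.25×3×0.0906 = 0.932 | 0.893 | 1.86 |
| 0.5 | switch day | 1 − 0.25×4×0.0906 = 0.909 | 0.884 | 1.82 |
| 1 | clean | 1 − 0.5×3×0.0906 = 0.864 | 0.786 | 1.73 |
| 1 | switch day | 1 − 0.5×4×0.0906 = 0.819 | 0.768 | 1.64 |

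The f = 0.5 rows suit the whole-day outcomes. At f = 0.25 the mean retained share is 0.955-0.966. Pooling days instead of averaging phase means changes these values by about 0.01 or less. The share of schedules in which a phase containing a switch day (phases 2 to 4) lasts only 7 days is 1 − C(22, 3)/2300 = 1 − 1540/2300 = 33%.

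**3. The SCS.** A momentary rating belongs to one state. If it is given after the visit, f = 0 and nothing is lost. The f = 1 rows (82-86%) apply only if every switch-day rating precedes the visit and is still filed under the new phase.

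**4. Group power.** The article's 16.35 subjects reproduces with a patient-level variance of 5.3 + 2×2/2 = 7.3, a difference of 2, two-sided 5%, 80% power and a noncentral t. With 20 patients, power is 88% at 2.0 points, 83% at 1.86, 81% at 1.82, 77% at 1.73 and 73% at 1.64.

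**5. Test walking in the step count.** The assumption is 1,000 extra steps per visit day (results scale linearly), with placebo visits included (1.18 per patient on average).

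| Day 1 | Added to A | Added to B | Mean B−A bias | SD across schedules |
|---|---|---|---|---|
| visit with tests | 107 per day | 107 per day | 0 | 23 |
| no visit | 62 per day | 107 per day | +45 per day | 23 |

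**The case against.** The strongest reply is that 2300 counts schedules and does not say which daily values enter a mean. No sentence assigns the switch day to the new phase, and an article may leave visit-day coding to the full protocol or SAP. This stands in part: the dilution is inferred, not stated. But the article does fix the allocation (every day in a phase) and the statistic (the mean of each phase). Followed as written, they set no day aside.

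A reader might infer three stronger claims that the documents do not support:

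- **Every visit day is mixed.** Placebo visits change nothing, so only the true switches are affected.
- **The primary outcome is diluted to about 1.73 points.** The SCS is momentary. The reminder for unrated days goes out between 7pm and 8pm, and a companion app item asks about removals over the day. This suggests, without proving it, that many ratings come after the visit. The 1.73 is an extreme case.
- **Test walking inflates the step result.** It occurs in both conditions and largely cancels in B−A. A mean bias towards Unity arises only if day 1 has no visit.

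It is also fair to say that any dilution runs towards no effect, and that half-day dilution leaves group power above the planned 80%.

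**Conclusion.** The point holds as a modest and inexpensive improvement. Three days, or four if the first disconnection falls on day 1, mix both states for steps, wearing time, sheath removals and fear of losing the prosthesis. If half of each such day is in the old state, about 91-93% of the B−A effect remains. For the SCS the possible loss runs from none to 14-18%, depending on when the patient rates relative to the visit, which the article does not fix. Test walking adds schedule-dependent noise to individual step contrasts (SD about 23 steps per day per assumed 1,000 extra steps per visit). It adds a mean bias of about +45 steps per day towards Unity only if day 1 has no visit.

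The old-state shares and the 1,000 steps are assumptions, as is counting the switch day in the new phase. The figure of 2300 is correct.

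**What to change.** 1. Have patients take the pedometer off during the L-Tests and 6-minute walk tests, at true and placebo visits alike.
2. For the whole-day outcomes, compute phase means without the first day of each phase, and apply the same rule to the observed schedule and to all 2300 reference schedules. The reference set and the minimum p of 0.0004 are then unchanged.
3. For the SCS on switch days, either use the time of rating to assign it to the state worn at that moment (the article lists time of data collection among the recorded items) or ask for it after the visit. The second option needs no special handling in the reference schedules, but may depart from the patient's usual rating time on those days.
4. State whether the first disconnection and a round of tests fall on day 1.

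The cost is a site instruction, a line in the analysis, and 3 of 50 daily values for the whole-day secondary outcomes (4 if day 1 is also dropped). No primary-outcome data need be lost.
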